### Data analysis plan

#### Main objective

The relationship between the score on the SCL-90-R prenatal global mental health self-report questionnaire, taking into account the other factors likely to influence the neurodevelopment score (sociodemographic, medical and psychological factors), and the child’s neurodevelopment score at age 1 on the standardised Bayley-4 test, will be assessed using multiple linear regression after checking the conditions of application. The main explanatory variable will be the SCL-90-R global score and the variable to be explained will be the child’s neurodevelopment score. The multivariate results will be reported using Beta coefficients and LSMEANS (adjusted means) and their 95% CI. The analyses will be conducted using SAS 9.4 and R 4.5.

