### Aims and hypotheses

#### Main objective

*Aim 1*: To characterise the impact of prenatal maternal psychological distress on neurodevelopmental outcomes at age 1 for children with cyanotic CHD who undergo neonatal open-heart surgery. We hypothesise that a higher level of maternal psychological distress as measured by the Symptom Check-List-90 R (SCL-90-R)^29^ will be associated with lower standardised neurodevelopmental scores as measured using the Bayley Scales of Infant and Young Child Development, Fourth edition (Bayley-4^30^) in children with CHD.

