#### Secondary objectives

*Aim 2*: To describe the evolution of maternal mental health (ie, anxiety, depression and psychological adjustment scores), from the antenatal period to the neonatal postoperative period (after cardiac surgery), and finally when the child with CHD turns 1 year. We predict that maternal psychological distress will decrease over time, as we expect that the most acute period of stress will be closest to the initial diagnosis of fetal CHD (T1, T2 and T3).

*Aim 3*: To identify the medical and sociodemographic factors associated with prenatal maternal psychological distress of women carrying a fetus diagnosed with cyanotic CHD. We hypothesise that lower maternal educational attainment and poor family support as well as fetal factors such as diagnosis of severe CHD (ie, univentricular heart) will be associated with worse prenatal maternal mental health outcomes (ie, overall mental health, anxiety and depression symptoms). The evaluation of scores obtained on self-report questionnaires (SCL-90-R,^29^ State-Trait Anxiety Inventory (STAI-Y),^31^ Coping Inventory for Stressful Situations (CISS),^32^ Edinburgh Postnatal Depression Scale (EPDS),^33 34^ Posttraumatic Stress Disorder Checklist for DSM-5 (PCL-5)^35 36^) completed by the mother will be analysed in relation to medical, sociodemographic and lifestyle factors.

*Aim 4*: To explore the mediating role of prenatal risk factors (ie, medical factors and maternal coping strategies, such as task-oriented, avoidant and emotional coping) in the association of prenatal maternal mental health (ie, distress, anxiety and depression) and neurodevelopment in children with CHD. We will also explore the potential interaction effects between sociodemographic factors and mental health on neurodevelopment in CHD. We hypothesise that expecting mothers with low socioeconomic levels of support and/or with maladaptive coping strategies (eg, avoidant, emotional reactivity) will experience the greatest effects of prenatal distress on their children’s neurodevelopmental outcomes at 1 year of age. The mediating role of medical and psychological antenatal factors (information extracted from the medical record, the interview and the information questionnaire) on the relationship between maternal mental health scores (SCL-90-R, STAI-Y, CISS, EDPS, PCL-5) and the child’s neurodevelopment (Bayley-4,^30^ Ages and Stages Questionnaire-Third Edition (ASQ-3)^37^) will be characterised.

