### Covariate measures

Medical, sociodemographic and lifestyle factors will be investigated. The sociodemographic factors collected will be maternal educational level, marital status, support systems (close family, access to medical care, level of geographical isolation, etc.), lifestyle characteristics regarding sleep, alcohol use and smoking and physical activity during pregnancy. We will derive indices of socioeconomic vulnerability from the French National Institute of Statistics and Economic Studies and include them in exploratory socioeconomic analyses. The medical factors collected will be type of CHD, gestational age, echocardiographic characteristics of the fetus (growth, associated cardiac anomalies), timing between first CHD fetal diagnosis and psychological assessments, maternal comorbidities including gestational diabetes, hypertension, placental abnormalities and any history of psychological or neurological symptoms for the mother as well as current and past pharmacological treatments. This information will be extracted from medical records, one semi-directive interview and the information questionnaire. Information on the child will also be collected by medical records and will include prenatal (spontaneous vs assisted reproductive technology, antenatal corticoid use or other neuroprotective therapies), perinatal (c-section birth, gestational age, birth weight, Appearance, Pulse, Grimace, Activity, Respiration (APGAR) score at 5 min, cardiac arrest, any other neonatal complications) and operative variables as well as current neurological diagnoses (ie, epilepsy, stroke, other events).

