#### Secondary objectives

##### Aims 2 and 3

In order to study changes over time (ie, evolution of maternal mental health) in the scores obtained on the self-report questionnaires (SCL-90-R, STAI-Y, CISS, PCL-5, EPDS) completed by the mother and to study changes as a function of medical, sociodemographic and lifestyle factors, a linear mixed model will be applied. This model takes into account the random effect induced by the analysis of three repeated measurements. The cofactors tested (fixed effects) will be the variables likely to influence the scores on these self-report questionnaires (medical, sociodemographic and lifestyle). The results of the linear mixed model are expressed for each factor in the form of a coefficient corresponding to the variation brought about by this factor on the basal score (intercept). A positive coefficient indicates a score-raising effect, while a negative coefficient indicates a score-lowering effect. For the time effect, the coefficient reflects the variation during the follow-up, while for the other factors, the estimate reflects the variation induced by the presence of the factor. The interactions between the co-factors and time will also be tested. A similar methodology will be applied for each score.

##### Aim 4

We will use a structural equation model to estimate simultaneously the relationships among maternal mental health (as captured by SCL-90-R, STAI-Y, CISS, PCL-5 and EPDS scores), prenatal factors (medical, sociodemographic and psychological) and child development (Bayley-4 and ASQ-3).

The structural pathways linking these three latent constructs, whereby maternal mental health impacts prenatal factors, which in turn influence the child’s development, while also allowing for a residual direct effect of maternal mental health on developmental outcomes.

We will quantify the mediating role of each block of prenatal factors by estimating the proportion of the effect of maternal mental health on child development that is transmitted through those factors. The model will be fitted using robust maximum likelihood estimation, with bootstrapping to derive CIs for indirect effects.

##### Aim 5

The GSI of the SCL-90-R will be used as an indicator of co-parent mental health. It is a standardised score with a T-score (mean 50, SD 10). The Bayley-4 cognitive score will be used as an indicator of neurodevelopment in children with CHD at age 1. This is an exploratory analysis, independent of the primary outcome.

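### The primary regression's covariate rule admits factors that Aim 4 treats as mediators, so the SCL-90-R coefficient may be a direct effect and not the overall impact named in Aim 1

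*Protocol article*

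**What the plan says.** All references are to the protocol article.

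- **Aims and hypotheses, Main objective.** Aim 1 is "To characterise the impact of prenatal maternal psychological distress on neurodevelopmental outcomes at age 1".
- **Data analysis plan, Main objective.** The GSI is the main explanatory variable for the child's Bayley-4 score in a multiple linear regression, "taking into account the other factors likely to influence the neurodevelopment score (sociodemographic, medical and psychological factors". The covariates are not itemised. Sample size and power considerations allows 10.
- **Secondary objectives, Aim 4 (aims).** The aim concerns the "mediating role of prenatal risk factors (ie, medical factors and maternal coping strategies, such as task-oriented, avoidant and emotional coping". A later sentence of the same aim speaks of "The mediating role of medical and psychological antenatal factors".
- **Data analysis plan, Aim 4.** The intermediate block of the structural equation model is "prenatal factors (medical, sociodemographic and psychological", in a model "whereby maternal mental health impacts prenatal factors, which in turn influence the" child's development. What is left for maternal mental health after that block is described as a residual direct effect.
- **Covariate measures.** The child's variables include "perinatal (c-section birth, gestational age, birth weight" and also Apgar score, neonatal complications, operative variables and current neurological diagnoses.
- **Procedures.** At T1 the mother completes the SCL-90-R, STAI-Y and CISS together.

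**The concern.** The covariate rule and the causal model use the same three labels: sociodemographic, medical and psychological. In the primary analysis these are factors to adjust for. In Aim 4 they transmit the effect. No sentence exempts mediators from the primary model, and none says that its coefficient is meant as a direct effect.

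Adjusting for a variable on the path takes out the part of the effect that runs through it. The Discussion presents maternal mental health as a modifiable target for later interventions. For that purpose the overall effect is the relevant one. A study following the rule as written could report a small adjusted coefficient and be read as showing little impact of prenatal distress, when part of that impact had been adjusted away.

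**Working it through.** **1. The plan's own figure.** Inputs from Sample size and power considerations: r = 0.45 (R² = 0.2025), 10 covariates, R² increase 0.20, alpha 5%, power 90%, 72 dyads. Taking the GSI first and adding 10 covariates:

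- f² = 0.20 / (1 − 0.2025 − 0.20) = 0.20 / 0.5975 = 0.335
- F test with 10 and 72 − 11 − 1 = 60 df, noncentrality 72 × 0.335 = 24.1
- Power = 0.905 at 72 and 0.899 at 71, so 72 is reproduced.

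This is a test of the 10 covariates added to the GSI, not of the GSI coefficient. A 1-df test of the GSI with an increment of 0.20 after 10 covariates needs 45 dyads if the covariates explain nothing, or 35 if they explain 0.20. The stated 90% is therefore no guide to power for an adjusted GSI coefficient.

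**2. Dyads available.** 87 × (1 − 0.20) = 69.6, so 69.

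**3. What the coefficient becomes.** The documents give no path values, so what follows is an assumed range. Take one standardised mediator M with GSI–M correlation a, M–outcome path b and direct effect c′ (signs dropped):

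- Total effect = c′ + ab = 0.45
- If a share m is mediated, ab = 0.45m, so c′ = 0.45(1 − m) and b = 0.45m / a
- m = 0.25: c′ = 0.45 × 0.75 = 0.338
- m = 0.50: c′ = 0.45 × 0.50 = 0.225

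**4. Power for that coefficient.** R² = c′² + b² + 2abc′, and the GSI's unique share is c′²(1 − a²). Example with a = 0.5, m = 0.5: b = 0.45; R² = 0.0506 + 0.2025 + 0.1013 = 0.354; unique share = 0.0506 × 0.75 = 0.038; f² = 0.038 / 0.646 = 0.059.

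The simulation used 69 dyads, 11 predictors (GSI, mediator, nine unrelated covariates), a two-sided 5% test and 20,000 replicates per row:

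| GSI–mediator correlation | Share mediated | Coefficient | Power |
|---|---|---|---|
| mediator left out | – | 0.45 | about 95% |
| 0.3 | 25% | 0.34 | 83% |
| 0.3 | 50% | 0.22 | 84% |
| 0.5 | 25% | 0.34 | 70% |
| 0.5 | 50% | 0.22 | 44% |
| 0.7 | 25% | 0.34 | 53% |
| 0.7 | 50% | 0.22 | 28% |

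A noncentral F calculation with noncentrality N × f² gives higher values (about 90% at 0.3; 78% and 51% at 0.5; 60% and 33% at 0.7), because it does not charge for estimating the other covariates. The pattern is the same. At a correlation of 0.3 power holds up because the mediator must then predict the outcome strongly (b = 0.375 or 0.75), which reduces residual variance.

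**5. Opposite sign.** If the indirect path opposes the total, for example with both paths of size 0.3, the adjusted coefficient is 0.45 + 0.3 × 0.3 = 0.54, away from zero.

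**The case against.** **The overlap is between categories, not variables.** The article names no primary covariate, and an itemised list may sit in a full protocol or SAP that is not shown. A reader might infer that the coefficient is certainly over-adjusted. The documents do not support that: all 10 covariates could turn out to precede the exposure. What stands is that the rule itself is stated here, has no timing condition, and conflicts with Aim 4.

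**Category membership does not make a variable a mediator.** The Aim 4 block includes sociodemographic factors, yet third-trimester distress cannot cause maternal education. CHD type, maternal psychological history and time since diagnosis are listed as medical factors and are plausible confounders. This stands. It means Aim 4's labels also need tidying, not that the primary rule is safe.

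**Bias toward zero is not established.** A reader might infer it from the mediation model. It needs an indirect effect of the same sign as the total and no unmeasured mediator–outcome confounding. The protocol's hypotheses and its plan to report a proportion transmitted imply the first but do not guarantee it.

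**Birth, operative and later variables are not mediators that Aim 4 names.** Aim 4 speaks of prenatal or antenatal factors. The case for keeping these variables out is that they arise after T1, not that the protocol declares them mediators. Likewise EPDS (T2) and PCL-5 (T3) come after T1, and nothing says either enters the primary model.

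**An adjusted association is a legitimate target.** Primary outcome measures and the sample size section speak of a relationship or an association. That is fair, but Aim 1 and the Discussion speak of impact, so the estimand needs to be stated.

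**Conclusion.** The point holds as a conflict within the protocol. The primary covariate rule, followed as written, can return a direct effect where Aim 1 asks for the overall impact, and r = 0.45 is a marginal correlation that does not describe such a coefficient. This is more than missing detail, because the rule is given and contradicts the protocol's own causal model.

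The size cannot be fixed from the article. If the indirect effect shares the sign of the total, the coefficient shrinks by exactly the mediated share. The loss of power ranges from moderate to severe with the GSI–mediator correlation. These figures assume a single mediator, a true total effect of 0.45, no confounding and 69 analysable dyads.

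**What to change.** In the Data analysis plan (Main objective):

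1. State that the primary estimand is the total effect of prenatal GSI on the Bayley-4 cognitive score.
2. Replace the rule based on influence on the outcome with a list, within the 10 covariates, of pre-exposure confounders or baseline predictors. Examples are maternal education or a socioeconomic index, CHD type, maternal psychological history and time since diagnosis.
3. Keep T1 STAI-Y and CISS out of the primary model. CISS measures the coping that Aim 4 names as a mediator. Aim 4's analysis uses both scales as indicators of maternal mental health itself.
4. Keep out every variable arising after T1 (birth, neonatal, operative, later neurological diagnoses). Use these in Aim 4 where they fit, or in a sensitivity model labelled as estimating a different quantity.
5. In Aim 4, separate background factors that distress cannot cause from the mediating block.

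If a direct effect is in fact intended, Aim 1 should say so and the planning value should be one for that coefficient.

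The cost is wording only, best settled before outcome data are seen. Residual variance may be somewhat larger without strong postnatal predictors.

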### Maternal mental health disorders and neurodevelopmental outcomes

Maternal mental health disorders are a significant concern in public health. Pregnancy and the post-partum period, which are particularly vulnerable in terms of biological and psychological changes, significantly increase the risk of developing a mental health disorder. Impaired maternal mental health is now recognised as one of the main peripartum and post-partum morbidities, with postpartum depression affecting up to 22% of women during the prenatal period or the first post-partum year.^20^ This percentage rises in the case of complicated or high-risk pregnancies, particularly when the fetus is diagnosed with CHD.^21^,^23^ These expecting women are faced with a multitude of sources of stress, ranging from invasive complementary examinations (eg, amniocentesis) to prognostic uncertainty about the health of the unborn child. In this context, the risk of maternal mental health deterioration dramatically rises, with a particularly high incidence of depressive states, anxiety disorders and post-traumatic stress disorder (PTSD) in the perinatal period.

In the absence of a specific fetal diagnosis, maternal mental health may be linked to changes in fetal brain development in utero, as well as to potential long-term cognitive, emotional and behavioural impairment in the child.^24^,^27^ Thus, maternal mental health appears to influence the neurodevelopment of the unborn child by modulating, in utero, both cerebral maturation and postnatal psychological attachment processes.^27^ More specifically, a recent study showed that perinatal maternal depression was related to the complexity or severity of the unborn child’s CHD, and that maternal stress and anxiety were associated with smaller cerebellar and hippocampal volumes in the fetus.^28^

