### Primary outcome measures

The primary outcome will be the relationship between the global mental health self-report questionnaire (SCL-90-R) at the prenatal evaluation (T1)^29^ and neurodevelopmental outcomes at age 1 measured via the Bayley-4.^30^ The SCL-90-R is a 90-item self-administered questionnaire assessing the psychological distress and mental health profile of adults. Each item is rated on a five-point Likert scale, from 0 (= not at all) to 4 (= extremely), according to the distress caused by each symptom. It assesses nine primary symptom dimensions: somatisation, obsessive-compulsive, interpersonal sensitivity, depression, anxiety, hostility, phobic anxiety, paranoid ideation and psychoticism. Three global indices provide measures of overall psychological distress: the global severity index (GSI), the positive symptom total and the positive symptom distress index (PSDI). The internal consistency of the SCL-90-R is satisfactory (α=0.54 to 0.84 for the French validation in adults).^28^ The GSI will be retained as the primary indicator of mental health in this study because it is the most sensitive indicator of the subject’s psychological distress, combining information on the number of symptoms and the intensity of psychological distress. The GSI is a standardised T-score (mean 50, SD 10).The cognitive score of Bayley-4^30^ will be used as the primary indicator of neurodevelopment in children with CHD at age 1 in this study. The Bayley-4 is a multidomain assessment tool of development in children, supporting early detection of developmental issues by measuring five key domains: cognitive, language, gross and fine motor and social-emotional. Bayley-4 scores are standardised and reported as standard scores (mean 100, SD 15). The Bayley-4 is the most widely used cognitive tests between the ages of 18 and 40 months^38^ and has solid psychometric qualities.^39 40^

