**Figure 1 F1:**
[figure not shown]
Study visit and data collection schedule. CHD, congenital heart disease; GA, gestational age.

At Time 2 (after surgery, before the child is discharged from hospital), a post-partum depression questionnaire (EPDS), an anxiety questionnaire (STAI-Y) and a coping scale (CISS) will be administered to the participants, at the most convenient time for them. Finally, an information note concerning the child’s next visit will be given to the parents along with parental consent for the child’s participation.

At Time 3, a follow-up consultation will be conducted with mothers and their 12 to 18 months old child. The mother will be offered a psychological state questionnaire (SCL-90-R), an anxiety scale (STAI-Y), a coping scale (CISS) and a post-traumatic stress scale (PCL-5). A neurodevelopmental examination using the standardised ASQ-3 and Bayley-4 tests will be conducted, including an assessment of the child’s behavioural and socio-emotional development, and their neurodevelopment (cognition, language, fine and gross motor skills, as well as psychosocial development). No measures will be collected for the co-parent at Time 3. Figure 2 summarises the measurements.

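### No stated model separates prenatal from postnatal maternal distress as predictors of the child's outcome, so an effect of continuing distress could be read as prenatal

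*Protocol article*

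**What the plan says.** Aim 1 of the protocol article is "To characterise the impact of prenatal maternal psychological distress on neurodevelopmental outcomes at age 1". Under Primary outcome measures the exposure is "the global mental health self-report questionnaire (SCL-90-R) at the prenatal evaluation (T1"), with the global severity index (GSI) as its indicator. The child's outcome is the Bayley-4 cognitive score. The Data analysis plan (Main objective) repeats that "The main explanatory variable will be the SCL-90-R global score and the variable to be explained will be" the child's score, and adjusts by "taking into account the other factors likely to influence the neurodevelopment score (sociodemographic, medical and psychological factors"). Covariate measures lists no postnatal maternal distress score.

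The Procedures text gives this schedule for the mother:

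| Time | Maternal scales listed |
|---|---|
| T1, prenatal | SCL-90-R, STAI-Y, CISS |
| T2, after surgery, before discharge | EPDS, STAI-Y, CISS |
| T3, 12–18 months | SCL-90-R, STAI-Y, CISS, PCL-5 |

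For T3 the wording is "The mother will be offered a psychological state questionnaire (SCL-90-R), an anxiety scale (STAI-Y), a coping scale (CISS"), followed by the PCL-5. The Bayley-4 belongs to the same follow-up.

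In the mixed model for Aims 2 and 3 the repeated maternal scores are the outcome. For Aim 4, the SEM measures maternal mental health by all five scales, lets it act on prenatal factors and through them on the child, "while also allowing for a residual direct effect of maternal mental health on developmental outcomes". The Discussion says that maternal mental health will be evaluated at three time points together with its effect on the child's neurodevelopment.

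**The concern.** Between T1 and the Bayley-4 lie birth, neonatal surgery and 12 to 18 months of care by the same mother. If distress persists, a T1 score is partly a marker of distress after birth. A T1 coefficient then looks the same whether the distress acted before birth, after birth, or both.

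The SEM does not resolve this. Its maternal construct includes two scales that the procedures text lists only after birth, carries no time index, and sits upstream of prenatal factors. Yet Aim 4 is about prenatal mental health. A postnatal effect would load on that construct and could be labelled prenatal.

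The distinction matters for the stated use. The Discussion wants to use knowledge about prenatal maternal stress to target prevention in fetal and congenital cardiology units. Whether distress acts before or after birth bears on when support should be offered, and the scores needed to examine this are already on the schedule.

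**Working it through.** **The plan's own figure.** Inputs from Sample size and power considerations: r = 0.45 (R² = 0.2025), 10 covariates, R² increase 0.20, power 90%, alpha 5%, 72 dyads. The 72 reproduces as a 10-df test of the covariates over R² = 0.2025:

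- f² = 0.20 / (1 − 0.2025 − 0.20) = 0.335
- λ = 72 × 0.335 = 24.1 on 10 and 60 df, power 0.905

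This point does not dispute the sample size. It uses n = 72 and r = 0.45 as the plan's own scale, ignoring sign.

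**Assumptions.** Let ρ be the correlation between T1 and postnatal distress. It is not in the documents, so a range of 0.3 to 0.8 is shown. The covariates are taken as uncorrelated with the scores. The 0.45, which the plan hypothesises for the T1 score, is assigned wholly to one period at a time.

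**Check A: the effect is wholly postnatal, the model has T1 only.**

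- Implied correlation of T1 with the outcome: r₁ = 0.45ρ
- f² = r₁² / (1 − r₁²), λ = 72f², F test on 1 and 60 df (T1 plus 10 covariates)
- Example, ρ = 0.6: r₁ = 0.27, f² = 0.0729 / 0.9271 = 0.0786, λ = 5.66, power 0.65

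**Check B: the effect is wholly prenatal, a postnatal score is added.**

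- Unique R² of T1 = 0.2025(1 − ρ²)
- f² = unique R² / (1 − 0.2025), F test on 1 and 59 df
- Example, ρ = 0.6: unique R² = 0.2025 × 0.64 = 0.130, f² = 0.1625, λ = 11.7, power 0.92

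| ρ (assumed) | A: implied r₁ | A: chance T1 is significant, n = 72 | B: power for T1, n = 72 | B: N for 90% power | Variance inflation 1/(1 − ρ²) |
|---|---|---|---|---|---|
| 0.3 | 0.135 | 21% | 98% | 49 | 1.10 |
| 0.5 | 0.225 | 49% | 95% | 58 | 1.33 |
| 0.6 | 0.270 | 65% | 92% | 68 | 1.56 |
| 0.7 | 0.315 | 79% | 85% | 84 | 1.96 |
| 0.8 | 0.360 | 90% | 71% | 118 | 2.78 |

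A simple-correlation (Fisher z) version of check A gives 48%, 63% and 77% at ρ = 0.5, 0.6 and 0.7, so the method matters little. In the setting of check A, a joint model with the postnatal score measured without error would flag T1 at the nominal 5%.

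**Reading.** Check A shows that a T1-only result is weak evidence on timing. Check B shows that a joint model is affordable: with 72 dyads it keeps at least 90% power for T1 up to ρ of about 0.6.

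**The case against.** The strongest objection is that postnatal distress follows T1 and may be caused by it. For the total effect of prenatal distress, leaving out a downstream mediator is correct. This stands, and the T1-only model should remain primary. A reader might infer that the primary regression is misspecified or must be adjusted for later distress; the documents do not support that. Elsewhere they also call the primary target a relationship or an association.

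A reader might also infer that postnatal distress enters no stated model. That is wrong: by the procedures text, the EPDS and PCL-5 in the SEM are postnatal scales. Nor does the regression explicitly exclude a postnatal score, since its psychological factors are not itemised. An article may leave that list to a fuller document, and this point does not rest on it. It rests on the stated exposure and the stated SEM paths.

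The Introduction might be read as naming attachment as a rival postnatal route. Its words are that maternal mental health acts "by modulating, in utero, both cerebral maturation and postnatal psychological attachment processes", which treats attachment as something modulated before birth.

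The plan excludes severe psychiatric disorder and collects the mother's psychological history and treatments. This may reduce chronic distress in the sample, but it does not separate the two periods.

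Finally, the size depends on an assumed correlation and on giving the full 0.45 to the postnatal period. That also stands.

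**Conclusion.** The point holds in this form: no stated model gives prenatal and postnatal maternal distress separate paths to the child's outcome, although Aim 1 speaks of impact and the Discussion looks to effects at three time points. The primary regression has the T1 score as its only stated exposure. The SEM mixes T1 scales with scales listed only after birth.

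The consequence is a risk of misreading. It is tempting to say that a postnatal effect would be reported as prenatal. The documents support only that it could be: under a purely postnatal effect of r = 0.45, the T1 score is significant in about 21% to 90% of studies of 72 dyads for ρ from 0.3 to 0.8, and in about 49% to 79% for ρ from 0.5 to 0.7. A smaller postnatal effect would lower these figures.

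The reading of the SEM relies on the procedures text; Figures 1 and 2 are not shown. The matter is worth correcting before analysis, but it does not invalidate the T1-only model as an estimate of a total association.

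**What to change.** 1. Keep the T1-only regression as primary and describe its result as the total association of prenatal distress with the child's score. Make no direct or in-utero claim from it alone.
2. Prespecify a secondary model for the Bayley-4 cognitive score with T1 and T3 GSI together.
3. Prespecify a supportive model with STAI-Y state anxiety at T1 and T2. T2 comes well before the developmental test, so it is less open to reverse causation. But it uses a different scale from the primary exposure and reflects only the hospital stay.
4. In the Aim 4 SEM, restrict the upstream construct to T1 scores and place T2/T3 distress in a separate, later node between T1 distress and the child's development.
5. State how the joint models will be read. A smaller T1 coefficient may mean mediation through later distress, or, with T3 GSI, reverse causation, because that score belongs to the same follow-up as the Bayley-4. Do not let the amount of shrinkage decide whether the result may be called prenatal: a prenatal effect fully mediated by later distress would fail such a rule.

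The cost is analysis-plan wording, two extra models and a somewhat larger SEM, with no new data collection. The joint models will have wider intervals: if the effect is truly prenatal at r = 0.45, power for T1 is about 95%, 92% and 85% at correlations of 0.5, 0.6 and 0.7.
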